#### *Demographic, clinical data*

Demographic, contact, clinical history and clinical examination data will be captured at the recruitment assessment.

#### *Drug history*

Regular use of prescription drugs will be recorded at recruitment, and the 6 and 12 month assessments.

#### *Smoking history*

Smoking history will be recorded at recruitment, and at the 6 and 12 month assessments.

#### *Height*

Height will be measured using clinic stadiometer at recruitment. If a remote assessment is being conducted, self reported height will be recorded.

#### *Weight*

Weight will be measured using clinic scales at recruitment. If a remote assessment is being conducted, self reported weight will be recorded.

#### *Heart rate*

Resting heart rate will be recorded at recruitment and the dose titration visits at week 1, 2, 3, 4 and the 6 and 12 month assessments. If a remote assessment is being conducted, these will be measured by the participant using a supplied digital sphygmomanometer.

#### *Blood pressure*

Blood pressure will be measured by a sphygmomanometer and recorded at recruitment and the dose titration visits at week 1, 2, 3, 4 and the 6 and 12 month assessments. If a remote assessment is being conducted, these will be measured by the participant using a supplied digital sphygmomanometer.

#### *Number of COPD exacerbations*

The primary outcome measure of the total number COPD exacerbations requiring antibiotics/oral corticosteroids whilst on study medication will be ascertained at the 6 and 12 month assessment. Attempts will be made to check GP records for all participants who do not attend for follow-up at 12 months and who do not complete the questionnaire. Participants will be encouraged to record any exacerbations on a 'reminder card' and to bring this to their follow-up assessments.

The ATS/ERS guideline definition of COPD exacerbation will be used: a worsening of patient's dyspnoea, cough and/or sputum beyond day-to-day variability sufficient to warrant a change in management [46]. The minimum management change will be treatment with antibiotics and/or oral corticosteroids. A minimum of two weeks

between consecutive hospitalisations/start of new therapy is necessary to consider events as separate. Severity will be ascertained for each exacerbation.

An operational classification of exacerbation severity will be used:

- Level I Increased use of their SABA
- Level II Use of OCS and/or antibiotics for exacerbation
- Level III Care by services to prevent hospitalisation
- Level IV Admitted to hospital

It can be challenging to differentiate between a COPD exacerbation and pneumonia. If the participant has been admitted to hospital and a definitive diagnosis is available, it will be possible to determine whether this is captured in the data set as an exacerbation, or as a hospital admission (with the diagnosis pneumonia).

If a participant is treated in primary care, a definitive diagnosis may not be available, unless the participant was referred for a chest x-ray. These cases will be captured as COPD exacerbations on the case-report form.

*Table 2 Schedule of study assessments*

| Assessment                                                                   | Recruitment | 1 week | 2 weeks | 3 weeks | 4 weeks | Month 6
(face to face) | Month 12
(face to face) | Post study
GP records | Post weaning/
final dose |
|------------------------------------------------------------------------------|-------------|--------|---------|---------|---------|---------------------------|----------------------------|--------------------------|-----------------------------|
| Assessment of Eligibility Criteria                                           | ✓           |        |         |         |         |                           |                            |                          |                             |
| For women of child-bearing potential – pregnancy test
(see section 9.6.1) | ✓           |        |         |         | ✓       | ✓                         | ✓                          |                          |                             |
| Written informed consent                                                     | ✓           |        |         |         |         |                           |                            |                          |                             |
| Confirmation that participant is content to continue in the trial            |             | ✓      | ✓       | ✓       | ✓       | ✓                         |                            |                          |                             |
| Demographic data, contact details                                            | ✓           |        |         |         |         |                           |                            |                          |                             |
| Clinical history                                                             | ✓           |        |         |         |         |                           |                            |                          |                             |
| Drug history                                                                 | ✓           |        |         |         |         | ✓                         | ✓                          |                          |                             |
| Smoking status                                                               | ✓           |        |         |         |         | ✓                         | ✓                          |                          |                             |
| Height*                                                                      | ✓           |        |         |         |         |                           |                            |                          |                             |
| Weight*                                                                      | ✓           |        |         |         |         |                           |                            |                          |                             |
| Pulse/heart rate**                                                           | ✓           | ✓      | ✓       | ✓       | ✓       | ✓                         | ✓                          |                          |                             |
| Blood pressure**                                                             | ✓           | ✓      | ✓       | ✓       | ✓       | ✓                         | ✓                          |                          |                             |
| Total number COPD exacerbations requiring
OCS/antibiotics                 |             |        |         |         |         | ✓                         | ✓                          | ✓                        |                             |
| Hospital admissions                                                          |             |        |         |         |         | ✓                         | ✓                          | ✓                        |                             |
| Health related quality of life                                               | ✓           |        |         |         |         | ✓                         | ✓                          |                          |                             |
| Disease related health status (CAT, BDI/TDI dyspnoea)                        | ✓           |        |         |         |         | ✓                         | ✓                          |                          |                             |
| HARQ (some centres only)                                                     | ✓           |        |         |         |         | ✓                         | ✓                          |                          |                             |
| Post bronchodilator lung function +                               | ✓           | ✓      | ✓       | ✓       | ✓       | ✓                         | ✓                          |                          |                             |
| Adverse events/drug reactions                                                |             | ✓      | ✓       | ✓       | ✓       | ✓                         | ✓                          |                          |                             |
| Major adverse cardiac events                                                 |             |        |         |         |         | ✓                         | ✓                          |                          |                             |
| Health care utilisation                                                      | ✓           |        |         |         |         | ✓                         | ✓                          |                          |                             |
| Patient Compliance                                                           |             | ✓      | ✓       | ✓       | ✓       | ✓                         | ✓                          |                          |                             |
| Telephone call to confirm cessation of study drug                            |             |        |         |         |         |                           |                            |                          | ✓                           |

- \* If remote assessment being conducted self reported height and weight will be recorded.
- \*\* If remote assessment being conducted these will be measured using a supplied digital sphygmomanometer.
- + During the COVID-19 pandemic, lung function (an aerosol generating procedure) will not be assessed.

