### **3.3 Primary endpoint/outcome**

The primary outcome measure will be the total number of exacerbations of COPD necessitating changes in management (minimum management change - use of oral corticosteroids and/or antibiotics) during the one year treatment period, as reported by the participant.

The primary economic outcome measure will be cost-per-QALY gained during the one year treatment period.

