#### *Hospital admissions*

The number of unscheduled hospital admissions whilst on study medication will be ascertained by questionnaire at the 6 and 12 month assessments. Emergency admissions consequent upon COPD will also be identified. Participants will be encouraged to record any hospital admissions on the reminder card, and bring this to their follow-up assessments. Attempts will be made to check GP records for all participants who do not complete the questionnaire and do not attend for follow-up at 12 months.

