#### *Mortality*

Deaths during the follow-up period will be reported as a SAE.

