## 9.2 Operational definitions for (S)AEs

In this trial:

- SAEs will be recorded from the time a participant consents to join the study until the end of the weaning period after the 12 month follow-up (see notes in section 8.7.2). Participants who withdraw from taking the study drug during the 12 month follow-up period will have SAEs recorded from the time the participant consents to join the study until 28 days after ceasing study medication. Participants who never start taking the study drug will have SAEs recorded for 28 days from the time they consent to join the study. All adverse reactions will be recorded for the same period of time described above.
- Hospitalisations for treatment planned prior to randomisation and hospitalisation for elective treatment of a pre-existing condition will **not** be considered or recorded or reported as an SAE. Complications occurring during such hospitalisation will also not be considered, recorded or reported as an SAE – unless there is a possibility that the complication arose because of the study medication (i.e. a possible adverse reaction).
- Exacerbations of COPD or hospital admissions as a consequence of exacerbations of COPD will **not** be considered as AEs or SAEs because they are primary and secondary outcomes for the trial. These will be recorded as part of the trial outcomes, but will not be considered or recorded or reported as AEs or SAEs. Confirmed cases of pneumonia should be captured as SAEs.

All other SAEs (including SARs) should be reported to the trial office.

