### 10.3 Statistical analysis plan

Statistical analyses will be according to the intention to treat principle with a per protocol analysis performed as a sensitivity. The per protocol analysis will exclude participants who were not compliant (at less than 70%) with their study medication. All analyses will be governed by this comprehensive SAP which will be agreed by the Trial Steering Committee (TSC) and approved by the independent Data Monitoring Committee (DMC) prior to any analyses being undertaken. Unless pre-specified, a 5% two-sided significance level will be used to denote statistical significance throughout. There will be no interim analyses undertaken. In line with other recent COPD trials it is not envisaged that the DMC will be monitoring the study in order to terminate it prematurely on finding evidence of overwhelming benefit – nor will they terminate it for futility.

The primary outcome - number of COPD exacerbations requiring antibiotics and/or oral corticosteroids in the 12 months after randomisation - will be compared between randomised groups using negative binomial regression with length of time in the study as an offset. Estimates will then be adjusted for centre and other baseline covariates that are known to be strongly related to outcome (e.g. age, smoking, COPD hospitalisations in year prior to study – these will be pre-specified in the SAP). Despite the patients being followed-up for a single year, some will withdraw early and, given their chronic illness, some will inevitably die. Use of an overdispersion parameter should improve the model estimates as it takes between patient variability in exacerbation rate into account. The negative binomial model assumes that each patient has their own underlying exacerbation rate which follows a Poisson distribution, but the expected rate is allowed to vary across patients according to a gamma distribution. The shape parameter from the gamma distribution explicitly represents the variability between patients. The negative binomial model coincides with the Poisson model when this dispersion parameter is zero. Assumptions of this model are that exacerbation counts are assumed to vary about means that differ for each patient, with means varying across the population. Hence, the negative binomial model more effectively accounts for increased exacerbation events amongst patients withdrawing early.

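### Section 7.6 words the primary outcome and unscheduled admissions as events while on study drug, while 10.3 counts 12 months from randomisation by intention to treat with time in study as offset; the two need one counting rule.

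*Protocol*

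**What the plan says.** The protocol describes the counting window for the primary outcome in three ways.

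- Section 7.6, Number of COPD exacerbations: "total number COPD exacerbations requiring antibiotics/oral corticosteroids whilst on study medication will be ascertained at the 6 and 12 month assessment".
- Section 10.3: "number of COPD exacerbations requiring antibiotics and/or oral corticosteroids in the 12 months after randomisation", compared by "negative binomial regression with length of time in the study as an offset". The governing principle is stated there too: "Statistical analyses will be according to the intention to treat principle with a per protocol analysis performed as a sensitivity".
- Section 3.3: "during the one year treatment period, as reported by the participant". This could mean the calendar year or the time actually on drug, so it settles neither reading.

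Section 7.6 uses the same restriction for admissions: "The number of unscheduled hospital admissions whilst on study medication will be ascertained by questionnaire". Section 10.3 analyses COPD admissions and all emergency admissions in the same way as the primary outcome.

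Section 7.10 asks participants withdrawn from treatment to stay on the trial schedule or to allow use of their records. Section 8.8 asks those who stop because they need a beta-blocker or an interacting drug to remain in follow-up. Section 10.3 ends a participant's contribution at loss to follow-up, not at stopping the drug.

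On deaths, section 7.6 says "Deaths during the follow-up period will be reported as a SAE" and section 9.5 requires all deaths to be reported. Section 9.2 says that participants who withdraw from the drug during the year "will have SAEs recorded from the time the participant consents to join the study until 28 days after ceasing study medication".

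**The concern.** The numerator in 7.6 and the denominator in 10.3 do not match. On the 7.6 wording an exacerbation after stopping the drug falls outside the outcome. On the 10.3 wording the time after stopping is still exposure. A participant who stops at month 1 and is followed for the year would contribute one month of countable events and twelve months of offset.

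This affects the primary estimate and the admissions outcomes. It also matters at the point of data collection: if sites follow 7.6 and do not record events after stopping, no later analysis decision can restore them for participants who attend and complete the questionnaire. The GP-record check described under this outcome in 7.6 is for those who do neither.

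**Working it through.** **Reproducing the plan's figures.** Inputs from 10.1: mean 2.22, SD 1.86, reduction to 1.89 (difference 0.33), 90% power, two-sided 5%. The normal formula gives 2 × (1.960 + 1.282)² × 1.86² / 0.33² = 667.6, so 668 per arm; the t-based version gives 669, as stated. Then 669 / 0.85 = 787.06, matching 787. The sample size is not in dispute.

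**Dispersion.** k = (1.86² − 2.22) / 2.22² = 1.2396 / 4.9284 = 0.25.

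**Mixed rule with no drug effect.** Let p be the share of an arm that stops the drug but stays in follow-up, and f the share of the year left after stopping. The mean on-drug share of the year is 1 − p·f. With the full year as offset:

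- apparent rate = 2.22 × (1 − p·f)
- apparent rate ratio = (1 − pB·f) / (1 − pP·f), with B for bisoprolol and P for placebo

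*Equal stopping, 15% at month 1 (f = 11/12).* 1 − 0.15 × 0.9167 = 0.8625, so each arm's rate falls from 2.22 to 1.91, about 14% too low. The ratio is 1.00 and the false-positive rate stays at 5%.

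*20% v 10%, month 1.* 0.8167 / 0.9083 = 0.90.

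*20% v 15%, month 1.* 0.8167 / 0.8625 = 0.95.

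*20% v 15%, mid-year (f = 0.5).* 0.900 / 0.925 = 0.97.

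**False-positive rates, 787 per arm.** Truncating the counts of stoppers lowers the mean and adds overdispersion. The effective dispersion in an arm is k* = (1 + k) × E[t²] / E[t]² − 1, where t is the on-drug share of the year. The standard error of the log ratio is the square root of the sum over arms of (1/rate + k*) / 787.

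| Stopping (bisoprolol v placebo) | k* by arm | SE | log ratio / SE | False positives (formula) | Range including simulations |
|---|---|---|---|---|---|
| 20% v 10%, month 1 | 0.50, 0.37 | 0.049 | −2.16 | 58% | 55-60% |
| 20% v 15%, month 1 | 0.50, 0.43 | 0.051 | −1.08 | 19% | 17-19% |
| 20% v 15%, mid-year | 0.31, 0.30 | 0.045 | −0.61 | 9% | 9-10% |

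Leaving out the extra overdispersion (SE 0.042) would give 71% and 25% for the first two rows, which is too high.

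**After the correction.** In simulated negative binomial fits (1,500 runs, 20% v 10%, f = 0.75, no drug effect), the mixed rule gave a ratio of 0.92 with 43% false positives. Counting all events over the 12 months with the same offset gave 1.00 and 6.1%, with simulation error of about 0.6 points. On-drug events with an on-drug offset gave 1.00 and 4.1%; that also removes the artefact but is not intention to treat.

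If placebo participants stop more often, the ratio moves the other way and looks like harm.

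**The case against.** The strongest reply is that the 7.6 phrase is loose shorthand for the treatment year. It does not say that later events are discarded, and much of the protocol points to 12-month capture. Sections 7.10 and 8.8 keep stoppers in follow-up. Section 7.6 lists a post-study examination of hospital and GP records for primary outcome data. Table 2 ticks exacerbations and admissions at 6 and 12 months and in post-study records with no on-drug limit. The lay summary says GPs will be asked about exacerbations in those who leave early. The analysis is by intention to treat. All this stands: a reader might infer that the protocol counts on-drug events and nothing else, but the documents do not establish that.

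A reader might also infer bias in favour of bisoprolol. The protocol gives one overall stopping figure, about 15%, and section 8.7.1 reports that in heart failure studies similar proportions on bisoprolol and placebo could not tolerate treatment. With equal stopping there is no rate-ratio bias under the null. That expectation is not a safeguard, since Table 3 lists bradycardia as very common on bisoprolol and the titration rules respond to heart rate and blood pressure. Even so, an imbalance remains an assumption. Month-1 stopping with every stopper staying in follow-up is near the worst case.

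Nor does the fault extend equally to deaths and major adverse cardiovascular events. Sections 7.6 and 9.5 already require deaths to be reported, and mortality is analysed by log-rank and Cox methods, not as a count over an offset. Section 7.6 sets no on-drug limit for major adverse cardiovascular events and provides a GP-record back-up.

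**Conclusion.** The wording conflict is in the current text and concerns the primary outcome, so it should be resolved. It appears twice in 7.6, for exacerbations and for unscheduled admissions, and section 3.3 does not resolve it.

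The consequence is conditional on two things. First, the 7.6 wording must govern what is counted while 10.3 governs the offset. In that case both arms' rates are understated, by about 14% at 15% stopping at month 1. Second, a distorted treatment effect under the null requires unequal stopping in number or timing. Under the assumed splits above, the ratio runs from 0.97 to 0.90, against a target of 0.85, with false-positive rates from about 9% to about 60%. The direction follows the imbalance, which the documents do not predict. Deaths need a clarification only, and major adverse cardiovascular events need no change.

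**What to change.** In section 7.6, for both exacerbations and unscheduled admissions, replace the on-medication phrase with: in the 12 months after randomisation, whether or not study medication is still being taken. Read section 3.3 in the same sense, and make sure data collection follows the rule; the case report form is not in the documents, so its wording should be checked. The offset in 10.3 can then stay as it is.

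If an on-treatment count is wanted, make it a supplementary analysis with on-treatment time as its offset.

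In section 9.2, add a clause that deaths are recorded to 12 months from randomisation for every participant regardless of treatment status, in line with sections 7.6 and 9.5.

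The cost is a wording amendment, a check of the collection forms, and record look-up for stoppers, which section 7.10 already provides for with consent. No extra participants are needed.

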#### *Hospital admissions*

The number of unscheduled hospital admissions whilst on study medication will be ascertained by questionnaire at the 6 and 12 month assessments. Emergency admissions consequent upon COPD will also be identified. Participants will be encouraged to record any hospital admissions on the reminder card, and bring this to their follow-up assessments. Attempts will be made to check GP records for all participants who do not complete the questionnaire and do not attend for follow-up at 12 months.

